#### **4.2.3 Clinical samples**

##### **4.2.3.1 Nasopharyngeal swabs**

- a) One nasopharyngeal swab is obtained prior to the administration of the study medication. A second nasopharyngeal swab is obtained 48 hours post administration of study medication. The swabs are stored in separate vials of STGGB medium and stored at -70 degrees prior to dispatch to the Menzies laboratory for processing.

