#### **4.3 Study size**

We plan to enrol 100 infants total. Children will be stratified by age (6 months and less and over 6 months), Indigenous status (Indigenous and non Indigenous) and site (Darwin and Townsville). The mean length of stay for bronchiolitis at Royal Darwin Hospital is 96 hours. To detect a mean difference of 24 hours in length of stay between treatment groups with an alpha of 0.05 and a power of 90%, the required sample size is 23 infants per group.

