#### 4.7 Microbiology/Virology

##### 4.7.1 Bacteriology of nasopharyngeal swabs

Swabs for microbiological analysis are stored in STGGB at -70 (in accordance with WHO guidelines). Presence of *Haemophilus influenzae*, *Moraxella catarrhalis* and *Streptococcus pneumoniae* will be identified using culture methods established in the Menzies laboratory. The antibiotic resistance phenotype will also be determined pre and post study medication administration.

Additionally, nucleic acids will be extracted from 0.2 ml of each nasopharyngeal swab specimen using the High Pure Viral Nucleic Acid kit (Roche Diagnostics, Australia), according to the manufacturer's instructions. Monospecific PCR and reverse transcriptase PCR (RT-PCR) method will be used to detect *Mycoplasma pneumoniae*, *Chlamydia pneumoniae* , coronaviruses , bocavirus  and human metapneumovirus (hMPV)  whereas multiplex PCR and RT-PCR will be used to detect adenovirus, parainfluenza (1, 2 3), influenza (A and B), and respiratory syncytial virus (RSV) . These methods have been previously validated in the QLD Paediatric Infectious Disease Laboratory.

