#### 4.8 Data analysis

**4.8.1 Primary outcome:** length of stay for bronchiolitis episode. The primary outcome (length of hospital stay) will be compared between infants receiving placebo or azithromycin using non-parametric analysis. Data within the Indigenous status will be analysed separately.

**4.8.2 Secondary outcome:** Length of time on supplemental oxygen; readmission to hospital within 6 months of this episode. All clinical secondary outcomes and laboratory data will also be analysed using non-parametric analysis. Categorical data will be compared using Chi square (or Fishers Exact).

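### The only post-dose swab is fixed at 48 hours with no provision for earlier discharge, so if azithromycin shortens stay as planned, second swabs are likely to be missing more often in that arm

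*Protocol*

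**What the plan says.** Section 4.2.3.1(a) of the protocol plans one swab before the study medication and one after it: "A second nasopharyngeal swab is obtained 48 hours post administration of study medication". It states no window, no swab at earlier discharge and no return visit. Section 4.6 follows infants through the medical chart to an acute end-point, more than 16 hours off oxygen and feeding well, and describes no later contact for swabbing.

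Section 4.7.1 uses the swabs for culture of three bacterial species and adds: "The antibiotic resistance phenotype will also be determined pre and post study medication administration". Section 4.8.2 says "All clinical secondary outcomes and laboratory data will also be analysed using non-parametric analysis". It names no carriage or resistance outcome.

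Section 4.3 gives the planning figures for stay: "The mean length of stay for bronchiolitis at Royal Darwin Hospital is 96 hours". The target is "To detect a mean difference of 24 hours in length of stay between treatment groups", "with an alpha of 0.05 and a power of 90"%, and "the required sample size is 23 infants per group". Planned enrolment is larger: "We plan to enrol 100 infants total".

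**The concern.** Whether a second swab exists depends on whether the infant is still in hospital 48 hours after the dose, and length of stay is the primary outcome. If the drug works as planned, more azithromycin than placebo infants will have left by then. The infants with a second swab would be a post-randomisation selection of longer stayers, and the selection would be stronger on azithromycin.

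Two things are at stake. Fewer second swabs mean less precise post-dose microbiology. And if carriage or resistance differs between early and late leavers, an arm comparison among swabbed infants is no longer a purely randomised one. Hypothesis (b) in section 3.1 makes such a difference plausible, because it attributes differences in recovery to co-infection. A later analysis plan can choose how to handle missing swabs, but it cannot recover swabs that were never taken.

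**Working it through.** **Inputs from the protocol.** Mean stay 96 h, taken as the placebo mean; planned difference 24 h, so 72 h on azithromycin; alpha 0.05; power 90%; 23 per group; 100 infants (all section 4.3). The swab is due 48 h after dosing (4.2.3.1).

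**Assumptions.** Two-sided test, since sidedness is not stated. About 50 per arm, since two of the four medication labels go to each treatment (4.2.2). The lag from admission to dosing is not stated; 0 to 24 h is used, guided by the exclusion in 4.1 of infants already on oxygen for more than 24 h.

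**Step 1: the plan's own figure.** No SD is given, so 23 per group cannot be reproduced from the stated inputs alone. Solving for the SD:

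SD = 24 / [(1.960 + 1.282) × √(2/23)] = 25.1 h (24.6 h with the t distribution).

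In reverse, n = 2 × (3.242 × 25/24)² = 22.8, which rounds up to 23. The stated size is coherent with an SD of about 25 h.

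**Step 2: share discharged before the swab.** With normal stays and equal SDs, P(stay < 48 + lag) = Φ[(48 + lag − mean)/25]. Ratios use unrounded shares.

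| Lag | Placebo (mean 96) | Azithromycin (mean 72) | Ratio | Missing per 50 |
|---|---|---|---|---|
| 0 h | Φ(−48/25) = 2.7% | Φ(−24/25) = 16.9% | 6.1 | 1.4 vs 8.4 |
| 12 h | Φ(−36/25) = 7.5% | Φ(−12/25) = 31.6% | 4.2 | 3.7 vs 15.8 |
| 24 h | Φ(−24/25) = 16.9% | Φ(0) = 50.0% | 3.0 | 8.4 vs 25.0 |

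**Step 3: sensitivity of the ratio** (lags 0 to 24 h).

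- SD 25 h, normal, equal coefficients of variation: 3.0 to 3.7.
- SD 25 h, gamma or lognormal: 3.2 to about 30. The largest values come from placebo losses of 1% or less and should not be leaned on.
- SD 36 h, all three distributions: 2.0 to 6.4.
- SD 48 h, all three: 1.6 to 3.3. With normal stays and equal SDs the absolute gap is still 15 points (30.9% − 15.9%, lag 0) to 19 points (50.0% − 30.9%, lag 24).
- SD 72 h, all three: 1.3 to 2.0.
- Exponential stays: about 1.2.
- No effect of azithromycin on stay: no differential loss.

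**Step 4: cost in precision.** For a difference in proportions with the same true proportion in both arms, the standard error grows by √[(1/n₁ + 1/n₂)/(2/50)].

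- Lag 0: √[(1/48.6 + 1/41.6)/0.04] = 1.06.
- Lag 24: √[(1/41.6 + 1/25)/0.04] = 1.27.

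So the standard error rises by about 6% to 27% at SD 25 h.

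**The case against.** - **No arm comparison of carriage or resistance is named.** Section 4.7.1 says only that the phenotype is determined before and after dosing, and 4.8.2 does not say that laboratory data are compared by arm. This stands: the comparison is implied, and it is secondary at most.
- **The loss is inferred from silence.** The protocol does not restrict the swab to inpatients, and the flow chart in 3.5 is not available to us, so a discharge step there cannot be excluded. This stands as a caution. The text that can be read points to no swab after discharge.
- **The multiple depends on assumptions.** A reader might infer that the loss is always at least twice as great on azithromycin. It is not: with lognormal stays and a coefficient of variation of 0.5 (SD 48 h on placebo), the ratio is 0.440/0.224 = 1.96 at a 12 h lag and 0.593/0.355 = 1.67 at 24 h. Stay is to be analysed non-parametrically, so the normal model deserves no special trust.
- **The 96 h mean may not fit the trial population.** It describes bronchiolitis at one hospital, while the trial enrols only infants needing oxygen. If they stay longer, fewer leave before the swab. This stands, and its size is unknown.
- **The bias cannot be quantified.** A reader might infer a definite spurious difference in carriage. With an assumed 50% carriage and no drug effect on carriage, a severity-carriage correlation of 0.4 gives 4 to 8 points, 0.2 gives 2 to 4, and zero gives none. The documents supply neither the carriage nor the correlation. The standard error of the arm difference would be roughly 10.5 to 12.6 points, so even the larger values lie below one standard error.

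These objections reduce the claim to possible bias in an implied secondary comparison. They do not remove the gap in the collection rule.

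**Conclusion.** The point holds as a gap in swab collection. Followed as written, section 4.2.3.1(a) is likely to leave early-discharged infants without a second swab, and if the planned 24 h reduction is real, this will happen more often on azithromycin. The size is about 3-17% against 17-50%, a ratio of about 3 to 6. That rests on an SD of about 25 h, normal stays and a dosing lag of 0 to 24 h. The ratio is 1.6 to 3.3 at SD 48 h, and about 1.2 to 2 for wider or exponential stays.

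The consequence is lost precision and data that can be biased; the documents do not show that they will be. Length of stay, time on oxygen and readmission do not depend on the swab and are unaffected. This is worth a cheap correction and does not threaten the trial's main conclusions.

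**What to change.** Reword 4.2.3.1(a) along these lines: *Take the second swab 48 hours after the study dose or immediately before discharge, whichever comes first, and record the time since dosing.* Report missing second swabs and dose-to-swab times by arm.

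For any arm comparison of post-dose microbiology, use all available second swabs as the main analysis and show the 48-hour swabs alone as a sensitivity analysis. Do not rely on adjustment for hours since dosing to remove the bias: for early leavers that time is set by discharge, which is itself post-randomisation.

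The cost is one sentence in the protocol and the matching ward procedure. The plan stays at two swabs per infant, and study staff already monitor the children daily (6.2). However, section 8 requires a trained team member to take the swab, so someone must be available before discharges that fall early. The statistical downside is that early leavers are sampled sooner after the dose, so dose-to-swab time may differ by arm. The recorded times make that visible, whereas a swab never taken leaves nothing to examine.

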#### **4.3 Study size**

We plan to enrol 100 infants total. Children will be stratified by age (6 months and less and over 6 months), Indigenous status (Indigenous and non Indigenous) and site (Darwin and Townsville). The mean length of stay for bronchiolitis at Royal Darwin Hospital is 96 hours. To detect a mean difference of 24 hours in length of stay between treatment groups with an alpha of 0.05 and a power of 90%, the required sample size is 23 infants per group.

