## 4 Study Design

All children admitted to the Paediatric ward RDH & TTH with a diagnosis of bronchiolitis will be identified and recorded on the study log. Eligibility of all children will be determined using the eligibility criteria in 4.1. Children enrolled in this study, eligible children not consented and children who do not meet the eligibility criteria will all be recorded on the study log.

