#### 4.2.1 Enrolment procedure

1. After obtaining informed consent, complete a consent form and give a copy of this and the information sheet to the carer.
2. Complete the enrolment form and the as much of the demographic and medical history as possible from the carer.
3. Use the date of birth and Indigenous status data to determine the treatment strata. There are 4 possible strata
  - Strata 1** Indigenous 6 months and less
  - Strata 2** Non Indigenous 6 months and less
  - Strata 3** Indigenous older than 6 months
  - Strata 4** Non Indigenous older than 6 months
4. Complete a chart notification sticker and stick in the child's medical chart

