#### 4.2.2 Randomisation and blinding of treatment allocation

This is a double-blind, randomised, placebo-controlled trial with concealed allocation. The study medications will be assigned the labels A, B, C or D (two labels assigned to placebo azithromycin and two assigned to azithromycin) by an independent person of the study at Menzies School of Health Research. Neither the study team (researchers, hospital staff) nor parents will know which treatment group (placebo or azithromycin) the infant has been assigned until the results have been analysed. Placebo azithromycin has been specifically manufactured by IDT Australia Limited (Melbourne, Victoria) and has a similar smell and taste to active azithromycin. The manufacture of placebo was

primarily for our NHMRC funded international study on bronchiectasis in Indigenous children.

The treatment allocation list has been computer generated by using stratified block randomisation. There are 4 sheets, each corresponding to the treatment strata. Treatment allocation has been concealed by black sticker. Upon enrolment an infant will be assigned to the next treatment on the appropriate stratified list and the treatment (A, B, C or D) revealed.

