**Procedure:**

1. After identifying the correct strata write the child's name and HRN on the next available line. The number refers to the child's study identification number.
2. Remove the sticker to reveal the study medication allocation (letter A, B, C or D). Record this on the child's chart notification sticker and on the enrolment form.
3. Treating physician to complete ABIS script to order medication/placebo on medication chart (dose 30mg/kg). Medication scripts are found in the study documents and are given to physician by ABIS study staff.
4. ABIS script taken to pharmacy by ABIS study staff and medication dispensed.
5. Take medication back to the paediatric ward and inform the nurse looking after the child that the child has been enrolled in the study.
6. For children enrolled on the weekends, please ensure that scripts are taken down to the Pharmacy before 1000hrs to ensure the pharmacy has enough time to dispense. Administer/supervise administration of first dose of medication.

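### Section 4.3 says randomisation is stratified by site, but the allocation procedure in 4.2 has only four lists, by age and Indigenous status

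*Protocol*

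**What the plan says.** Section 4.3 of the protocol names three stratification factors, each with two levels: "Children will be stratified by age (6 months and less and over 6 months), Indigenous status (Indigenous and non Indigenous) and site (Darwin and Townsville".

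By contrast, the operational text names two. Section 4.2.1 instructs staff: "Use the date of birth and Indigenous status data to determine the treatment strata. There are 4 possible strata". It then lists all four, each a combination of Indigenous status and age; none mentions a hospital. Section 4.2.2 reports that "The treatment allocation list has been computer generated by using stratified block randomisation" and that "There are 4 sheets, each corresponding to the treatment strata". Allocation is taken in order: "Upon enrolment an infant will be assigned to the next treatment on the appropriate stratified list and the treatment (A, B, C or D) revealed". The numbered procedure that follows has staff find the stratum, write the child on the next free line and remove the sticker. Of that line it says: "The number refers to the child's study identification number".

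The trial recruits at two hospitals. Section 4 opens: "All children admitted to the Paediatric ward RDH & TTH with a diagnosis of bronchiolitis will be identified and recorded on the study log". No visible text says where the sheets are kept, whether each hospital has its own set, or how study numbers are kept distinct between hospitals. The flow chart in 3.5 is not reproduced in the text available, so it cannot settle the matter.

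**The concern.** The stratification factors are a stated property of the design, and the protocol gives two accounts of them. The strata, the sheets and the line-by-line procedure are all fixed in the protocol, so this is not detail deferred to a statistical analysis plan.

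At stake is whether the arms are balanced within each hospital. Length of stay, the primary outcome, can depend on local discharge practice and patient mix. Section 4.3 gives a mean stay for Royal Darwin Hospital only (96 h), so the protocol does not show that the two hospitals are alike on this outcome. Staff and auditors also need a single reading of which list applies to which child, because the list line supplies the study number.

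**Working it through.** **1. Count of strata.**

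| Source | Factors | Strata |
|---|---|---|
| 4.2.1, 4.2.2 and procedure | age (2) x Indigenous status (2) | 4, on 4 sheets |
| 4.3 | age (2) x Indigenous status (2) x site (2) | 8 |

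With 100 infants (4.3), the mean stratum size is 100/4 = 25 or 100/8 = 12.5. The stated 23 per group and the total of 100 do not depend on which applies.

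**2. Site imbalance if the four lists are shared by both hospitals.**

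Inputs:
- From 4.3: 100 infants. Two labels per arm (4.2.2) imply 1:1 allocation, so 50 per arm.
- Assumed, because the protocol gives no figure: the number at Townsville, n_T = 30 (range 20 to 50), and a site difference in mean stay of 24 h.

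The SD of (active minus placebo) at Townsville is approximately sqrt(n_T x (1 - n_T/100)).

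- n_T = 30: sqrt(30 x 0.70) = 4.58 infants.
- 95% limit: 1.96 x 4.58 = 9.0 infants. With 30 infants the difference must be even, so actual splits near this limit are 19 v 11 or 20 v 10.
- Mean absolute difference: about 0.80 x 4.58 = 3.7 infants.

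The shift in the arm comparison is (difference / 50) x site difference in stay.

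| n_T | SD | Typical (mean absolute) shift | 95% limit |
|---|---|---|---|
| 20 | 4.0 | 0.80 x 4.0 / 50 x 24 = 1.5 h | 1.96 x 4.0 / 50 x 24 = 3.8 h |
| 30 | 4.58 | 0.80 x 4.58 / 50 x 24 = 1.8 h | 1.96 x 4.58 / 50 x 24 = 4.3 h |
| 50 | 5.0 | 0.80 x 5.0 / 50 x 24 = 1.9 h | 1.96 x 5.0 / 50 x 24 = 4.7 h |

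Every shift is proportional to the assumed site difference. At 12 h the middle row becomes 0.9 h and 2.2 h; with no site difference it is zero.

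**3. Simulation check.** The settings were 100 infants, equal age-by-Indigenous cells, assumed block size 4 or 8, assumed Townsville share 20%, 30% or 50%, and 3,000 runs per setting. The ranges are across settings.

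| Result | 4 shared lists | 8 site-specific lists |
|---|---|---|
| Mean absolute arm difference at Townsville | 3.2 to 4.1 | 1.4 to 2.1 |
| 95th percentile | 8 to 10 | 3 to 5 |
| Chance of a difference of 6 or more | 16% to 29% | 0.1% to 3.4% |
| Mean absolute arm difference, whole trial | 1.3 to 1.9 | 1.9 to 2.8 |

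At a 30% share the simulated mean with shared lists is 3.7 to 3.8, in line with the formula. Site-specific lists reduce the site imbalance but do not remove it: 3 to 5 infants still correspond to 3/50 x 24 = 1.4 h up to 5/50 x 24 = 2.4 h. They also loosen overall balance slightly, because more blocks are left incomplete.

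**4. Other arrangements consistent with the text.** If each hospital holds its own four sheets, allocation is blocked within stratum at each hospital. Site is then balanced up to incomplete blocks, and the figures in step 2 do not apply.

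**The case against.** The strongest reply is that 4.2.1 and 4.2.2 are ward instructions. Staff at one hospital have no site to choose, so they see four strata and four sheets, while 4.3 describes the whole trial. Four sheets at each of two hospitals would give the eight strata of 4.3, and 4.2 would be incomplete rather than contradictory. Concealed paper sheets are also hard to share between two cities, which makes separate sets plausible. This reading is possible, but no visible text states it. Section 4.2.2 counts four sheets in total, not four per hospital.

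A reader might go further and infer that study numbers will be duplicated and that one hospital's revealed letters will predict the other's. The documents do not support that. Both would need identical sheets to have been copied to both hospitals, and nothing says so. Even then a letter does not disclose the treatment, because there are two coded labels per arm, assigned by an independent person. Nor can these harms be added to the site imbalance above. Imbalance of that size needs one shared sequence, whereas copied sheets would keep each hospital blocked.

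It is also fair to say that the 24 h site difference has no source and simply equals the target effect, that 4.3 h is a 95% limit and not the expected shift, and that age and Indigenous status are already stratified. Section 3.4.1 itself links Indigenous status to longer stay. These points limit the size of the harm; they do not reconcile the sections.

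**Conclusion.** The allocation procedure as written does not deliver the site stratification that 4.3 claims. The mismatch of four strata against eight rests on the text alone and needs no assumption.

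The consequence is conditional. If the four lists are shared, the typical shift is about 1.8 h and the 95% limit about 4.3 h, against a 24 h target (4.3/24 = 18%). Both figures assume 30 Townsville infants and a 24 h site difference. If each hospital has its own set, the defect is an omission in 4.2.

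A reader might infer that the primary comparison is biased or invalid. It is not: blocked randomisation within four shared lists is valid and keeps the arms close in total number. The cost is lost precision and an allocation procedure with more than one reading. Severity is moderate; this does not have to be resolved before the trial can be relied on.

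**What to change.** Make 4.2.1, 4.2.2 and 4.3 agree, in one of two ways.

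- **Site is a stratum.** State that there are four independently generated lists per hospital, eight in total, with study number series that do not overlap. If each hospital already holds its own set, say so in 4.2 and confirm that the sets are not copies of one another.
- **The lists in use are not by site.** Remove site from the stratification sentence in 4.3, and state in 4.2 how one set of lists serves two hospitals.

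In either case, specify that the primary non-parametric comparison in 4.8.1 is stratified by or adjusted for the randomisation factors and site, for example with a stratified rank test such as van Elteren's. This recovers most of what chance site imbalance would cost, whichever lists were used.

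The cost is a text correction and possibly new lists for one hospital. Eight lists halve the mean stratum size from 25 to 12.5, so more blocks will be incomplete. The 23 per group and the total of 100 are unchanged.

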#### **4.4 Refusal to participate**

Participation in the study is completely voluntary. A participant may choose to refuse to participate in the study. Parents will be reassured that the care of their child will not be compromised in any way by not participating.

#### **4.5 Withdrawal of Participant**

Participation in the study is completely voluntary. A participant may choose to withdraw at any stage without giving reason.

#### 4.6 Clinical assessment

Children enrolled in this study will be managed by hospital staff according to standard clinical practice for the management of bronchiolitis. They are not exempt from receiving any care or management protocol specified by the attending physician.

A standardised sheet will be used to collect clinical data. Demographic information and medical history will be obtained from the primary care-giver and from hospital records. The primary and secondary outcome measures (described below) will be monitored from the medical chart until the acute study end-point has been reached (defined as >16 hours off supplemental oxygen and infant is feeding well). Clinical assessment data includes oxygen requirement and level, physiological measurements for clinical severity score (respiratory rate, accessory muscle use, degree of wheeze), other physiological measurement (temperature, heart rate), requirement for other therapies (IV fluids, nutrition, antibiotics). In addition routine investigatory parameters (FBC and chest x-ray findings) will be recorded.

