#### **3.2. Aim**

Assess the efficacy of a single dose of Azithromycin (30mg/kg) to

- a) Improve the clinical course of moderate to severe bronchiolitis (assessed by supplemented oxygen requirement and length of hospital stay).
- b) reduce the risk of further respiratory illness within 6 months of this bronchiolitis episode.
- c) Profile the immunopathology of bronchiolitis in the presence and absence of co-existing respiratory infections.

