### **3.4 Background and rationale**

#### **3.4.1 Infants with bronchiolitis in the NT: burden and outcomes**

Bronchiolitis (with or without pneumonia) is the most common cause of admission in children aged under 12-months. In a Central Australian study, we described a prevalence of approximately 190 per 1000 children for RSV bronchiolitis. The prevalence of all causes of bronchiolitis would indeed be higher. In our setting, co-existent pneumonia is high in Indigenous children and, at the Royal Darwin Hospital (RDH), the majority of children with bronchiolitis are also treated with antibiotics. The co-existent pneumonia is likely related to the high carriage rate and early acquisition of respiratory pathogens in Indigenous children compared to non-Indigenous children. We have reviewed 100 charts of children hospitalised with bronchiolitis at the RDH and found that the readmission rate of Indigenous children for their next bronchiolitis episode within 6-months was 30% (unpublished). As the majority of these children hospitalised for bronchiolitis are retrieved from remote communities, the impact of the illness and costs plus social dislocation is significant. Furthermore recurrent lower respiratory tract infection is an independent significant risk factor for the later development of bronchiectasis and lower pulmonary function in later years. In addition the severity of the hospitalised episode (oxygen requirement and length of hospital stay) were also risk factors for development of bronchiectasis. In our retrospective chart review we found that Indigenous infants hospitalised with bronchiolitis had more severe bronchiolitis than non-Indigenous infants (unpublished). In Indigenous infants, the severity score at presentation, number of days requiring oxygen and length of hospitalisation were all significantly worse or longer than in non-Indigenous infants ( $p=0.0001$ ,  $0.004$ ,  $0.001$  respectively). Thus any intervention that is efficacious in reducing the

severity of bronchiolitis and/or readmission for bronchiolitis in Indigenous children would be beneficial in both short and long term outcomes.

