### 6.1 Safety parameters

Safety profile, as measured by the incidence, intensity, and relationship to study drug of adverse events and serious adverse events.

An **adverse event** is any untoward medical occurrence experienced by the participant while undergoing treatment in a clinical trial, and up to one week after the dose of Study medicine. Adverse events include temporary, moderate discomfort and disability to the participant.

A **serious adverse event** is defined as any event that is fatal or life threatening is permanently disabling to the participant, any admission to hospital, or an overdose that requires additional medical management

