### 6.2 Methods of assessing safety parameters

Side effects of Azithromycin are rare. Those listed in MIMS Annual 2001 included: nausea, vomiting, diarrhoea, or abdominal pain. Rare but potentially serious side effects listed are angioedema and cholestatic jaundice.

The children enrolled in the study have been admitted to TTH and RDH and as such are monitored according to hospital protocol. The child's progress is monitored daily by the study staff via the medical chart and the Nursing Unit Manager.

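### Aim (b), the six-month outcome in section 4.8.2 and the monitoring rule in section 4.6 contradict one another on what is measured and until when

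*Protocol*

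**What the plan says.** Four places in the protocol bear on the six-month question.

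- Section 3.2, aim (b): the single dose is to "reduce the risk of further respiratory illness within 6 months of this bronchiolitis episode". The target is respiratory illness, and nothing limits it to illness that leads to admission.
- Section 4.8.2 lists two clinical secondary outcomes: time on supplemental oxygen, and "readmission to hospital within 6 months of this episode". No cause of readmission is specified.
- Section 4.6: "The primary and secondary outcome measures (described below) will be monitored from the medical chart until the acute study end-point has been reached". The acute end-point is "defined as >16 hours off supplemental oxygen and infant is feeding well".
- Section 3.4.1 gives the only six-month rate in the protocol, from a chart review at one of the two hospitals: the "readmission rate of Indigenous children for their next bronchiolitis episode within 6-months was 30" per cent.

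The timeline in section 3.6 has a row that combines recruitment and follow-up, but gives neither the length nor the method of follow-up. The flow chart in section 3.5 is a figure that could not be read for this review.

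**The concern.** There are two separate conflicts.

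The first is about time. Section 4.6 points forward to the outcomes in section 4.8 and gives all of them one stopping rule. That rule suits length of stay and oxygen time. It cannot suit readmission, which by definition happens after the index stay. Staff who follow section 4.6 as written would close data collection before the second secondary outcome can occur.

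The second is about content. The aim is respiratory illness, the outcome is readmission without a named cause, and the background rate is readmission for bronchiolitis. Readmission of unspecified cause is too broad for the aim, because it admits non-respiratory admissions. It is also too narrow, because respiratory illness managed outside hospital does not count.

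At stake is whether the comparison under aim (b) can be interpreted. If all readmissions are counted, those that the drug would not change dilute the contrast. If the cause is settled only at analysis, the definition is open to choice after the data are seen. If ascertainment is not planned, it may differ from infant to infant.

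**Working it through.** **Step 1. Set the statements side by side.**

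| Place | Event | Window |
|---|---|---|
| 3.2, aim (b) | Respiratory illness, admitted or not | 6 months |
| 4.8.2 | Readmission, cause not stated | 6 months |
| 4.6 | All primary and secondary outcomes | Until the acute end-point |
| 3.4.1 (background) | Bronchiolitis readmission, Indigenous children | 6 months |

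An infant reaches the acute end-point on criteria judged during the index admission. Readmission requires discharge first. The window in 4.6 therefore does not overlap the period in which the 4.8.2 outcome can arise. This needs no calculation.

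**Step 2. Is there a planning figure to reproduce?** Not for this outcome. The sample size in section 4.3 rests on a 24-hour difference in length of stay, and no readmission rate enters it. Nothing in 4.3 changes under this point.

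**Step 3. Illustrate what the choice of definition does.**

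Inputs:
- control respiratory readmission 30%: borrowed from the 3.4.1 background rate, which covers only Indigenous children and bronchiolitis readmission, so its use for all infants is an assumption;
- treated rate 15%: assumed;
- unrelated readmission *q*, the same in both arms and independent of respiratory readmission: assumed at 5%, 10% or 20%;
- 50 infants per arm: the 100 planned in section 4.3, with equal allocation assumed;
- two-sided alpha 0.05: sidedness assumed.

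The all-cause rate in an arm with respiratory rate *p* is 1 − (1 − *p*)(1 − *q*). For *q* = 10%:

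- control: 1 − 0.70 × 0.90 = 0.370
- treated: 1 − 0.85 × 0.90 = 0.235
- risk ratio: 0.235 / 0.370 = 0.64, against 0.15 / 0.30 = 0.50 for respiratory readmission alone

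Power = Φ{[|p₁ − p₂| − 1.96 √(2p̄(1 − p̄)/n)] / √([p₁(1 − p₁) + p₂(1 − p₂)]/n)}, where p̄ is the mean of the two rates.

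- 30% vs 15%: (0.150 − 1.96 × 0.0835) / 0.0822 = −0.167, so power is 43%
- 37% vs 23.5%: (0.135 − 1.96 × 0.0919) / 0.0909 = −0.496, so power is 31%

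| *q* | Control | Treated | Risk ratio | Power |
|---|---|---|---|---|
| 0 | 30% | 15% | 0.50 | 43% |
| 5% | 33.5% | 19.25% | 0.57 | 36% |
| 10% | 37% | 23.5% | 0.64 | 31% |
| 20% | 44% | 32% | 0.73 | 23% |

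The direction is the same throughout. The size depends on rates that the protocol does not give.

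**The case against.** The best defence is that section 4.6 describes acute clinical assessment. The word acute implies a later phase, the timeline mentions follow-up, and the section 3.5 flow chart may show the six-month step. On that view the sentence is loosely drafted and nothing is lost. This stands against any claim that aim (b) cannot be answered, which a reader might infer. It does not remove the conflict, because the sentence expressly covers the secondary outcomes and one of them is six-month readmission.

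It can also be said that section 4.8.2 is silent on cause rather than committed to all causes, that the background sets readmission in a respiratory context, and that an analysis plan could settle the cause. The silence is fairly noted: the dilution applies only if the outcome is read as it stands, without restriction. But the aim and the outcome are both fixed in the protocol and they differ. A later analysis plan also cannot supply data that the written collection rule leaves out.

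The power figures rest on assumptions, and power is low under either definition for an outcome on which the trial was not sized. That is correct, and it is why they serve only as illustration.

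Three further readings are tempting and not supported:

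- That the 30% is a planning rate. It is background in section 3.4.1 and plays no part in section 4.3.
- That readmissions to other hospitals would be missed. Many children come from remote communities, but nothing says that readmissions are sought only at the two study hospitals.
- That adverse events are under-counted in the arm that goes home sooner, because they count "up to one week after the dose of Study medicine" while section 6.2 describes inpatient monitoring. Section 6.2 does not call this the only capture, and the section 6.3 reporting flow chart was not available. The window also runs from the dose, whereas length of stay runs from admission, so the two cannot be compared directly.

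**Conclusion.** The point holds as an unreconciled contradiction among sections 3.2, 4.6 and 4.8.2. The conflict over the monitoring window and the mismatch between aim and outcome follow from the text and need no assumption. The documents do not show that six-month data go uncollected. Nor would readmission of any cause be useless: it would answer aim (b) in part, with some non-respiratory events counted and respiratory illness outside hospital left out.

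The size of the dilution is not known. With the assumed 30% vs 15%, 50 per arm and 10% unrelated readmission, the risk ratio moves from 0.50 to 0.64 and power from 43% to 31%. Over 5% to 20% unrelated readmission, power runs from 36% down to 23%. The primary outcome and the sample size are unaffected.

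**What to change.** - **Section 4.8.2:** define the outcome as readmission for respiratory illness within 6 months of this episode, with the cause classified from the discharge diagnosis by someone blind to allocation. Report all-cause readmission as supportive.
- **Section 4.6:** apply the acute end-point rule to length of stay and oxygen time only. State that readmission is ascertained for every infant at 6 months from hospital records, and name the records to be searched.
- **Section 3.2, aim (b):** state that respiratory illness is measured as respiratory readmission, so that illness treated outside hospital is acknowledged as not captured.
- **Section 3.5:** if the flow chart already shows a six-month step, bring the text into line with it.

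The cost is wording, one record search per infant and blinded classification of cause. The drawbacks are that a discharge diagnosis can be ambiguous, so a simple rule for mixed diagnoses should be written beforehand, and that respiratory readmissions alone give fewer events than all readmissions. Keeping the all-cause figure as supportive lets a reader see whether the classification drives the result.
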